### 2.3 Sample size calculation

Two-hundred and twenty-five individuals who meet the selection criteria for the study will be recruited. The estimated sample size needed is n = 63 participants per condition considering a moderate effect size (Cohen’s d = 0.5) for the difference between the active arms at post-intervention compared to the control group for the primary variable (i.e., FIQR score) with an alpha = 0.05 and 1-b power = 0.80. With an expected dropout rate of 20%–25%, the final sample size is estimated at 75 individuals per arm. The effect size used for the sample size calculation corresponds to the average effect size for multicomponent interventions in FM vs. control group (Nüesch et al., 2013). Previous RCTs evaluating the FIBROWALK intervention indicated effect sizes between d = 0.4 (Serrat et al., 2021a) and d = 1.83 (Serrat et al., 2020). Using as a reference previous studies of the group evaluating the effect of different non-pharmacological treatments in FM patients on blood values of immuno-inflammatory markers (Andrés-Rodríguez et al., 2019; Montero-Marin et al., 2020), it is estimated that a sample size of 40 subjects per arm will be sufficient to be able to detect changes in the evaluated variables.

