### 2.5 Procedure and randomization

The recruitment of participants will be carried out in two ways: 1) consecutive recruitment from consultation by the rheumatologists of the HUVH Central Sensitivity Syndromes Specialized Unit and 2) by screening a list of patients (with contact telephone number) corresponding to patients who contacted the Unit during the last 6 months. The clinicians involved in the project (i.e., MA and MS) will proceed to carry out the telephone screening and those who meet the selection criteria of the study will be invited to participate. After obtaining written informed consent, the instrument battery -including clinical and economic measures-described below will be administered (online assessment). Two research assistants will coordinate the study assessments to ensure an adequate understanding of all administered self-reported measures. Random assignment of participants to study arms will be executed after baseline assessments as recommended by the CONSORT guidelines (Schulz et al., 2010). Once written consent and baseline assessment have been completed, study participants will be given a unique personal code and randomized using randomization software (1:1:1 ratio). The computer-generated randomization will apply a permuted block design to ensure that the groups are balanced taking biomarkers substudy eligibility criteria (No=Not meeting criteria for biomarkers substudy; Yes = Meeting criteria) into account. The randomization list will be stored in an encrypted file on a password-protected computer in the clinical trials supervisor’s office to assure concealment of allocation. Participants will be informed of their group allocation by the administrative personnel, who will send a notification *via* email.

Patients who meet the selection criteria for the biomarkers substudy will be rescheduled 3–5 days after the first assessment to obtain blood samples (up to the required N of 40 subjects per arm). Fasting blood extractions will be performed in a pre-set time window (8a.m.–10a.m.) to reduce circadian variability in the levels of the biomarkers evaluated. In order to limit the effects of medication on the study variables, patients will be asked to refrain from taking any occasional anti-inflammatory drugs in the 72 h prior to blood sampling.

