The research assistants, who will be blinded to randomization, will coordinate the three subsequent clinical assessments: at 6 weeks, at post-intervention and at 6 months after the baseline assessment (follow-up). The same procedure as in baseline will be followed for the collection of biological samples at post-intervention, respecting the pre-set time interval.

The study will be organized in two consecutive periods with six study groups (i.e., 2 TAU, 2 FIBRO-Out, 2 FIBRO-On) conducted in parallel in each period. All the groups will include 18–20 participants (i.e., FIBRO-On, FIBRO-Out, TAU), so the N = 75 is expected to be reached at the end of the study.

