#### 2.11.1 Analysis of clinical effectiveness

The primary effectiveness analysis will be conducted on an intention-to-treat (ITT) basis with the FIQR total score as a primary clinical endpoint (McCoy, 2017) and by linear mixed-effects regressions with restricted maximum likelihood (REML). REML accounts for the correlation between repeated measures for each individual and produces less biased estimates of variance parameters when using small sample sizes or unbalanced data (Egbewale et al., 2014). No imputation of missing data will be conducted, since it has been reported that multiple imputation is not necessary for all types of missing data (missing completely at random, missing at random, and missing not at random) before computing longitudinal mixed model analysis (Twisk et al., 2013). Unstandardized regression coefficients (B) and 95% confidence intervals (95% CIs) will be computed for the ‘group x time’ interaction between groups at 6-week, post-treatment and 6-month follow-up assessments. Cohen’s d will be calculated for each pairwise comparison, using the pooled baseline SD to weight the differences in the pre–post mean values and to correct for the population estimate (Morris, 2008). The rule of thumb for effect size interpretation will be the classical cutoffs for Cohen’s d of 0.20 = small, 0.50 = medium, and 0.80 = large. All secondary clinical endpoints will be analyzed using the same statistical procedure. Benjamini–Hochberg correction for multiple comparisons will be applied to control for false rate discovery (Glickman et al., 2014). All the analyses will be replicated using a “completers” approach including all participants who finished the study, and a per-protocol approach, taking into account only those patients who attended at least 75% of the sessions (9 out of 12).

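### The primary FIQR effect reads as a difference in change from baseline, which is unbiased but less precise than a baseline-adjusted or common-baseline contrast

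*Protocol article*

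**What the plan says.** Section 2.11.1 makes the FIQR total score the primary endpoint, analysed by intention to treat with a linear mixed model fitted by REML. The effects to be reported are unstandardised coefficients with 95% confidence intervals for the group-by-time "interaction between groups at 6-week, post-treatment and 6-month follow-up assessments". Cohen's d is to be built on differences in pre–post means, scaled by the pooled baseline SD. All secondary clinical endpoints follow the same procedure. The section does not say whether arm means at baseline are free or held equal, and it lists no covariates.

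Table 3 shows FIQR at baseline, 6 weeks, 12 weeks and 6 months. Section 2.5 places randomisation after the baseline assessment and describes a "permuted block design to ensure that the groups are balanced taking biomarkers substudy eligibility criteria". It also says: "The study will be organized in two consecutive periods with six study groups".

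The sample size in section 2.3 rests on a simpler quantity, "considering a moderate effect size (Cohen’s d = 0.5") "for the difference between the active arms at post-intervention compared to the control group", "with an alpha = 0.05 and 1-b power = 0.80".

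Elsewhere the article does name covariates. Section 2.11.3 lists the baseline outcome among optional control variables for the economic model, and section 2.11.4 names antidepressant status as a conditional covariate for the biomarkers.

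**The concern.** With four FIQR measurements and three post-baseline interaction coefficients, baseline is the reference visit inside the outcome vector. If arm means at baseline are left free, each coefficient is a difference in change scores. Because randomisation follows baseline, any baseline difference between arms is chance. A change-score contrast subtracts that chance difference in full, whereas a model that adjusts for baseline, or holds the arms to a common baseline mean, removes only the part that predicts the outcome.

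Precision is at stake, not validity. The primary contrast, and every secondary contrast analysed the same way, would be less precise than the collected data allow. The power in section 2.3 also refers to a comparison of post-intervention values, and the planned contrast reproduces that power only under a condition on the baseline-to-follow-up correlation that the article does not discuss.

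**Working it through.** **Inputs from the article.** d = 0.5, alpha 0.05, power 0.80, 63 per arm before dropout, 75 per arm after it (section 2.3). Expected dropout is 20%–25% ("With an expected dropout rate of 20%–25%, the final sample size is estimated at 75 individuals per arm"), so 75 × 0.80 = 60 or 75 × 0.75 = 56 remain per arm.

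**Assumed.** rho, the correlation of baseline with post-intervention FIQR, is not given; 0.3 to 0.8 is used. The FIQR SD is taken as equal at both visits and set to 1. The test is two-sided with the normal approximation.

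**Step 1: reproduce the plan's figure.** n = 2 × (1.960 + 0.842)² / 0.5² = 62.8, rounded up to 63. This matches "The estimated sample size needed is n = 63 participants per condition". The calculation uses the variance of a single post-intervention value and no baseline information.

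**Step 2: variance per patient under each contrast.**
- Post-intervention value only: 1
- Change from baseline: 2(1 − rho)
- Baseline-adjusted or common baseline mean: 1 − rho²
- Ratio of adjusted to change: (1 − rho²) / [2(1 − rho)] = (1 + rho)/2, which is below 1 whenever rho is below 1

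**Step 3: condition for matching the design power.** 2(1 − rho) ≤ 1 requires rho ≥ 0.5. At exactly 0.5 the change contrast has the design variance, and power is 80.1% with 63 per arm, 78.2% with 60 and 75.4% with 56.

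**Step 4: power with 60 per arm.** Power = Φ(0.5 / √(2V/60) − 1.960), with V from Step 2.

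| rho | V change | V adjusted | Ratio | Power, change | Power, adjusted | n per arm for 80% (change / adjusted) |
|---|---|---|---|---|---|---|
| 0.3 | 1.40 | 0.91 | 0.65 | 63.9% | 81.9% | 88 / 58 |
| 0.5 | 1.00 | 0.75 | 0.75 | 78.2% | 88.5% | 63 / 48 |
| 0.7 | 0.60 | 0.51 | 0.85 | 94.2% | 97.0% | 38 / 33 |
| 0.8 | 0.40 | 0.36 | 0.90 | 99.1% | 99.5% | 26 / 23 |

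For example, at rho 0.5 the adjusted contrast gives 0.5 / √(2 × 0.75/60) = 3.162; 3.162 − 1.960 = 1.202, and Φ(1.202) = 0.885.

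**Step 5: does the randomisation stratum or the period matter for precision?** A factor that is constant over time cancels in a within-person change. A small REML simulation checked this: 60 simulated two-arm trials, 60 per arm, four visits, rho about 0.5, complete data, random intercept, stratum effect 0.4 SD, period effect 0.2 SD.
- Group-by-time model: SE of the 12-week contrast 0.1818
- Stratum and period main effects added: 0.1818
- Stratum and period added by time: 0.1816
- Common baseline mean instead: 0.1582, a variance ratio of (0.1582/0.1818)² = 0.76, close to the 0.75 of Step 2
- Common baseline mean plus stratum and period: 0.1569

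The precision gain comes from the handling of baseline. The stratum and period add almost nothing.

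**The case against.** The strongest reply is that a condensed article need not list every fixed effect. Section 2.11.1 excludes no covariate and does not say that baseline means are free. A common-baseline model also yields visit-specific group-by-time coefficients, so the full plan may already contain the fix. This stands in part: silence is not exclusion. The article does, however, fix the form of the effect, and its effect-size definition is built on pre–post differences. The plain reading is an unadjusted change contrast.

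Second, that contrast is unbiased and widely used, and it keeps its type I error. That stands in full.

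Third, the size of the loss hangs on a correlation that the article does not give. That also stands: at rho 0.7 the gain is 3 percentage points, and at 0.8 it is under one. The figure of 60 evaluable per arm also treats dropouts as contributing nothing, although the mixed model uses whatever visits they have.

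A reader might infer two stronger points. One is that leaving out the randomisation stratum or the period costs power or inflates standard errors. Step 5 shows that it does not for the planned contrast, and section 2.5 does not describe period as a randomisation factor. The other is that the trial discards power it had budgeted for. Section 2.3 counted on no gain from baseline adjustment, and with rho of 0.5 or more the planned contrast gives at least the design power for the same evaluable number.

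**Conclusion.** The point holds as a matter of efficiency. On the plain reading of section 2.11.1, the primary FIQR contrast is a difference in change from baseline, and its variance is 2/(1+rho) times that of a baseline-adjusted or common-baseline contrast. In power terms, with 60 per arm and d = 0.5, the shortfall is about 18 points at rho 0.3, 10 at rho 0.5 and 3 at rho 0.7. Below rho 0.5 the planned contrast has less power than the comparison used to size the trial. With 60 per arm at rho 0.5 it gives 78.2%, and baseline adjustment lifts that above 80%.

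This rests on free baseline means by arm, equal SDs at baseline and follow-up, and assumed values of rho. It does not put the validity of the planned analysis in doubt. It is a free improvement, because baseline FIQR is collected from every participant before randomisation.

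**What to change.** State in the analysis plan one of two equivalent choices for FIQR:
- a mixed model for the 6-week, 12-week and 6-month values with baseline FIQR by time as a covariate; or
- a constrained longitudinal model with baseline in the outcome vector and a single baseline mean common to all three arms.

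In either case report the arm-by-time contrasts at each post-baseline visit. Include biomarker-substudy eligibility as a fixed effect so that the analysis follows the randomisation; little precision gain should be expected from it (0.1582 to 0.1569 in the simulation, with period also added). A period term is optional. Use the same approach for the secondary outcomes. Align the Cohen's d definition by dividing the adjusted contrast by the pooled baseline SD, so that the reported effect size and the model estimate describe the same quantity.

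The cost is a change of wording. No new data, visits or participants are needed.

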The objectives of the On&Out study are 1) to examine the effectiveness and cost-utility of adding the FIBROWALK intervention in online or in outdoors format to TAU in the management of patients with FM for improving functional impairment (primary outcome) and pain, fatigue, depressive and anxiety symptoms, perceived stress, central sensitization, physical function, sleep quality and perceived cognitive dysfunction (secondary outcomes); 2) to identify pre–post differences in levels of different physiological variables (i.e., immune-inflammatory markers and BDNF levels) and correlate these changes with those observed at self-report measures and 3) evaluate the role of psychological process variables considered to be potential mediators of the interventions from a theoretical point of view (i.e., kinesiophobia, pain catastrophizing, psychological inflexibility in pain and pain knowledge) and the evaluated physiological variables as mediators of long-term clinical improvements. For the sake of personalized treatment in FM, the design of the present study will allow us to explore whether certain patient profiles or baseline psychobiological characteristics may help predict the short- and long-term clinical response to the specific evaluated treatments.

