In addition, to assess clinical significance of the improvement on the primary outcome (FIQR), all the participants will be allocated into the categories of “responder” and “non-responder” by using the criteria of presenting at least a 20% reduction in the pre–post FIQR total score or not, respectively (Bennett et al., 2009). This classification will be used to compute the number needed to treat (NNT) for each treatment when compared to the others. The NNT refers to the estimated number of patients who need to be treated with a new proposed treatment (i.e., rather than the control comparison treatment) for one additional patient to benefit. A 95% CI for each NNT will be calculated. This index allows findings from RCTs to be more meaningful to clinicians. Furthermore, in order to explore potential predictors of treatment response in each intervention arm, t-tests and χ2-tests will also be performed to assess potential baseline differences in sociodemographic, clinical and physiological variables between responders vs. non-responders within the FIBRO-Out and FIBRO-On arms. Finally, baseline differences between participants who completed all study assessments and those who did not will also be evaluated (with *t* and *χ2*-tests) to detect any potential attrition bias.

The differences between FIBRO-On and FIBRO-Out on perceived clinical improvement (assessed with PGIC and PSIC) and on treatment expectation/opinion (i.e., with the CEQ) will be computed using χ^2^ tests and Student’s *t* tests, respectively.

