This study has some strengths that should be highlighted. The inclusion of a relatively large sample and of a comprehensive set of measures will allow us to compare the short term (pre-post) and long-term (6 months) effectiveness of two different formats of the FIBROWALK multicomponent program on core FM outcomes and psychological process measures. Furthermore, the identification of cost-effective interventions is a priority for the national health system, especially for highly prevalent conditions such as FM. This study will evaluate for the first time the cost-effectiveness of two formats (which can be particularly useful in the pandemic and post-pandemic era) of a multicomponent intervention for FM. In this sense, it is necessary to introduce new practices in the provision of healthcare services to improve efficiency in the use of resources. In this regard, boosting treatments aimed at changing lifestyles and patterns of cognition and behavior (as it is aimed in FIBROWALK) constitutes a strategy of financial sustainability as, in the long-term, it will allow an extension of the culture of health understood holistically and, therefore, a decrease in the burden of disease on society as a whole. Our study will also explore immune-inflammatory and neuroprotective pathways behind the efficacy of the evaluated treatments, and will combine clinical and process measures which may lead to a better characterization of the syndrome, to new therapeutic interventions, and to a better prediction of treatment response in order to better determine what works for whom in the field of personalized medicine. Finally, it is also worth mentioning that the present RCT will involve six therapists (three psychologists and three physiotherapists) in delivering the FIBRO-Out intervention; doing so (instead of only one therapist delivering the therapy) can provide more realistic and generalizable results (Ost, 2014) which can be useful for the future implementation of these interventions in healthcare systems.

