Up to date, there is no study assessing the cost-effectiveness of multicomponent approaches for FM neither evaluating the long-term effectiveness of such type of interventions in online or outdoor formats. If one or both treatments evaluated in this present RCT (i.e., FIBRO-On and/or FIBRO-Out) shows to be effective and cost-effective they should be included as part of the standard of care for treating FM. Furthermore, since both interventions are, per definition, conducted out of the hospital settings, they could also be safely administered in the context of future pandemics, and (in the particular case of the FIBRO-On program) in circumstances of low accessibility to effective treatments for FM (e.g., in remote areas), highly congested healthcare services and/or low availability of clinical resources. The On&Out project is also aimed at determining psychophysiological patient profiles which can be useful for identifying potential treatment beneficiaries (i.e., treatment responders) beforehand which may in turn improve healthcare resources allocation. Last but not least, the present study may also help us in deepening our knowledge on which psychological and physiological mechanisms underpin the clinical effects of non-pharmacological interventions in FM, further contributing to the potential detection of novel therapeutic targets.

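### The search for predictors of response compares responders with non-responders inside each active arm, without TAU, so it cannot separate prognostic factors from factors that predict benefit

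*Protocol article*

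**What the plan says.** Section 2.11.1 of the protocol article sets the response rule and the predictor analysis together.

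- **Response rule.** For the FIQR, "all the participants will be allocated into the categories of" responder and non-responder, according to "presenting at least a 20% reduction in the pre–post FIQR total score or not". This covers all three arms and feeds the NNT.
- **Predictor analysis.** "in order to explore potential predictors of treatment response in each intervention arm", t-tests and chi-square tests are to "assess potential baseline differences in sociodemographic, clinical and physiological variables between responders vs. non-responders within the FIBRO-Out and FIBRO-On arms". TAU plays no part in this step.
- **Purpose.** The last paragraph of section 1.3 says the design allows exploring whether baseline profiles "may help predict the short- and long-term clinical response to the specific evaluated treatments". The Discussion (section 3) speaks of better prediction of response "in order to better determine what works for whom in the field of personalized medicine", and later of patient profiles useful for "identifying potential treatment beneficiaries (i.e., treatment responders) beforehand which may in turn improve healthcare resources allocation".

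The article contains no test of a baseline variable by treatment arm. The mediation models in section 2.11.2 concern change in process variables, not baseline moderators.

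**The concern.** A responder is a patient whose FIQR falls by at least 20%. A beneficiary is a patient whose FIQR falls further than it would have under TAU. The Discussion treats the two as the same, but only a comparison with TAU separates them. Someone who would have improved by 20% on TAU is a responder in the FIBRO-On arm without owing that response to FIBRO-On.

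A baseline variable linked to improvement whatever the treatment will differ between responders and non-responders in each active arm. Under this plan it would be listed as a predictor of response to the programme. Separate tests in the two active arms also cannot show who should receive one format rather than the other, because significance in one arm and not in the other is not evidence of a difference.

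What is at stake is the personalised-treatment aim. The trial randomises a control arm that could serve that aim, and the planned analysis does not use it.

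**Working it through.** **Inputs from the article.** Effect size: "considering a moderate effect size (Cohen’s d = 0.5" (section 2.3). Sample size: 75 per arm; with 20% dropout, 75 × 0.8 = 60. Response: at least a 20% fall in FIQR. The predictor analysis states no figure of its own. The sample size does reproduce: 2 × (1.96 + 0.84)² / 0.5² = 62.7, i.e. 63 per arm.

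**Assumed, not in the article.** FIQR mean 65; SD 18 before and after; pre-post correlation ρ from 0.5 to 0.8; one baseline covariate x, independent of baseline FIQR, with standardised effect 0.3 on the post score in both arms. Every treated patient gains 0.5 SD = 9 points, so x predicts no difference in benefit.

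**Step 1: who responds.** With B the baseline and Y the post score, response means 0.8B − Y ≥ 0.
- Mean of 0.8B − Y, active arm: 0.8 × 65 − (65 − 9) = −4.
- Mean, TAU: 0.8 × 65 − 65 = −13.
- SD: 18 × √(0.64 + 1 − 1.6ρ). At ρ = 0.6 this is 18 × √0.68 = 14.84.
- Response rate at ρ = 0.6: active Φ(−4/14.84) = 39%; TAU Φ(−13/14.84) = 19%.

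**Step 2: the prognostic covariate within an arm.** Its correlation with 0.8B − Y is, in size, 0.3/√(1.64 − 1.6ρ). Dichotomising multiplies this by φ(z)/√(p(1 − p)), where p is the response rate and z the matching normal quantile. At ρ = 0.6, active arm: 0.364 × 0.787 = 0.286. Fisher's z statistic is atanh(0.286) × √57 = 2.22, so the chance of p < 0.05 is about Φ(2.22 − 1.96) = 60%.

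**Step 3: baseline FIQR within an arm.** Its correlation with 0.8B − Y is (0.8 − ρ)/√(1.64 − 1.6ρ). It shrinks as ρ rises, is zero at 0.8 and changes sign above that.

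Closed-form chance that the within-arm test is significant, 60 per arm:

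| ρ | x, active arm | x, TAU | baseline FIQR, active arm |
|---|---|---|---|
| 0.5 | 51% | 43% | 51% |
| 0.6 | 60% | 49% | 31% |
| 0.7 | 73% | 57% | 13% |
| 0.8 | 87% | 66% | 5% |

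**Step 4: simulation of the same set-up.** The covariate is flagged in roughly 52% to 90% of trials in the active arm and 43% to 64% in TAU. Baseline FIQR is flagged in about 53%, 31%, 13% and 5% at ρ = 0.5, 0.6, 0.7 and 0.8; the figures move by a few points if simulated scores are capped at 0 and 100. The treatment-by-covariate interaction on the post score, adjusted for baseline FIQR, is significant in about 4% to 6%.

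**Step 5: other assumptions.** With SD 15 or 20, ρ 0.5 or 0.7 and 60 or 75 per arm, the covariate is flagged in 52% to 85% of trials (active) and 41% to 70% (TAU), and the interaction in 4% to 6%. With a covariate effect of 0.2, 0.3 or 0.4 at ρ = 0.6, the active-arm figure is 32%, 61% or 88%.

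**The case against.** Several points on the other side have weight.

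- **The percentages are not false-positive rates of the planned test.** A prognostic covariate really does differ between responders and non-responders, so the test is detecting something true. This stands. The figures count as errors only when the result is read as differential benefit. Section 2.11.1 and section 1.3 speak of response; the benefit reading comes mainly from the Discussion, which equates responders with beneficiaries.
- **A reader might infer that the analysis finds prognosis instead of benefit.** The article does not support that. A true effect modifier would also separate responders from non-responders, mixed with prognosis. The defect is that the two cannot be told apart.
- **A reader might infer that the 20% rule makes baseline FIQR a predictor through regression to the mean in any event.** It does not. The effect depends on the slope of post on baseline, and the article gives neither SD nor correlation. A larger post SD weakens it further: with 21 instead of 18, the slope at ρ = 0.6 is 0.6 × 21/18 = 0.70, and baseline FIQR is flagged in about 10% of trials.
- **The aim is hedged.** The article says profiles may help or can be useful, and ties no allocation rule to this analysis. That limits the severity but does not make the estimate answer the question.
- **Interaction tests are weak.** For a moderator of 0.3 SD per SD and residual SD 0.8 (both assumed), the standard error is 0.8 × √(2/n). Approximate power is 54% at 60 per arm and 39% at the 40 per arm planned for biomarkers, or 32% at 32 (40 less 20%), before any multiplicity correction. This is a real cost. A larger sample would not rescue the within-arm test, since it would flag prognostic variables more often.

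**Conclusion.** The point holds in this form: the planned predictor analysis cannot distinguish prognostic factors from factors that predict benefit, while the article's stated purpose is the latter. That follows from leaving TAU out and needs no numerical assumption. The size does rest on assumptions: under a uniform effect, a covariate of standardised strength 0.3 is flagged in roughly half to nine tenths of trials within an active arm, and nearly as often in TAU, which receives no programme. The regression-to-the-mean component is secondary and conditional, material at a pre-post correlation of 0.5 to 0.6 and small or absent at 0.7 to 0.8.

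The analysis is labelled exploratory. The primary mixed model, the NNT, the mediation models and the cost-utility analysis are untouched. It should be corrected, but it does not threaten the trial's main conclusion.

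**What to change.** In the analysis plan:

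1. Prespecify a short list of candidate baseline moderators.
2. For each, test the treatment-by-covariate interaction on continuous FIQR, adjusted for baseline FIQR, for FIBRO-On vs TAU, FIBRO-Out vs TAU and FIBRO-On vs FIBRO-Out.
3. Apply Benjamini–Hochberg over the list, report interaction estimates with 95% confidence intervals, and label the results exploratory effect modification.
4. Keep the 20% responder rule for the NNT.
5. If the within-arm responder comparisons are retained, report them as prognostic only, and do not use them to support statements about treatment beneficiaries or what works for whom.

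The cost is wording; no new data are needed. The downside is low interaction power, above all for biomarkers measured in only 40 per arm, so fewer predictors will be reported.

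### Predictors of response are sought only inside the two active arms, so the analysis cannot separate prognosis or regression to the mean from modification of the programme's effect

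*Protocol article*

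**What the plan says.** Section 2.11.1 classifies every participant, in all three arms, as a responder or non-responder according to "presenting at least a 20% reduction in the pre–post FIQR total score or not, respectively". Across arms, the stated use of this classification is the number needed to treat.

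The section then turns to prediction, "in order to explore potential predictors of treatment response in each intervention arm". The method is univariable: "t-tests and χ2-tests will also be performed to assess potential baseline differences", and the contrast is "baseline differences in sociodemographic, clinical and physiological variables between responders vs. non-responders within the FIBRO-Out and FIBRO-On arms". TAU is not part of it.

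No other section supplies the missing contrast. The group-by-time term in 2.11.1 estimates average effects, and the path models in 2.11.2 test mediation.

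Three places say what the results are for. The aims at the end of section 1.3 hope that baseline profiles may "help predict the short- and long-term clinical response to the specific evaluated treatments". The Discussion speaks of determining "what works for whom in the field of personalized medicine" and later of "identifying potential treatment beneficiaries (i.e., treatment responders) beforehand", which it links to allocating healthcare resources.

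**The concern.** Within a single arm, every patient receives the same treatment. A baseline variable associated with improvement there may be prognostic (those patients would have improved anyway), may reflect regression to the mean, or may modify the treatment effect. Only a comparison with a randomised control arm separates the third from the first two. The trial has that arm, with the same baseline measures and the same responder classification, and the predictor analysis does not use it.

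Baseline FIQR is especially exposed because the responder rule is built from it. Keeping the outcome continuous would not help: a within-arm analysis of change has the same ambiguity.

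At stake is the personalised-treatment message. Equating responders with beneficiaries could point an online or outdoor programme towards patients who would have improved equally under TAU, and away from patients who gain just as much from it.

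**Working it through.** **Inputs from the protocol article.** Section 2.3: d = 0.5, alpha 0.05, power 0.80, 63 per arm before dropout, 75 per arm recruited, 20–25% dropout. Section 2.11.1: the 20% rule. Section 2.8.1: FIQR runs from 0 to 100.

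**The plan's own figure.** With a two-sided alpha assumed, 2 × (1.960 + 0.842)² / 0.5² = 62.8, so 63 per arm reproduces. Numbers analysed: 75 × 0.80 = 60 and 75 × 0.75 = 56.25. The simulations use 58 or 60 per arm.

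**Assumed, because the article does not give them.** Baseline FIQR mean 60–65 and SD 15–20, equal SDs before and after, the pre–post correlation r, and the strength of any prognostic variable.

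**Direction for baseline FIQR.** Write post = μ + r(pre − μ) − δ + e, where δ is a benefit identical for everyone and e has SD σ√(1 − r²). Then

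P(post ≤ 0.8 × pre | pre) = Φ{ [(0.8 − r)·pre − μ(1 − r) + δ] / [σ√(1 − r²)] }.

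The coefficient of pre has the sign of 0.8 − r. The probability of response therefore rises with baseline for r < 0.8, is flat at 0.8 and falls for r > 0.8. The constant benefit δ does not change the sign, and neither do μ and σ. The change in the probit index per baseline SD is (0.8 − r)/√(1 − r²).

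**Size for baseline FIQR.** Simulation of 2,000 trials per setting, 60 per arm, mean 65, SD 17, and a benefit of 0.5 SD for every patient, so that no true predictor of benefit exists. Entries are the share of trials with p < 0.05.

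| r | index per SD | active arm, t-test as planned | same t-test in TAU | baseline-by-arm interaction |
|---|---|---|---|---|
| 0.5 | 0.3/0.866 = 0.35 | 49–50% | 37–39% | 4–6% |
| 0.6 | 0.2/0.800 = 0.25 | 26–28% | 20–22% | 4–6% |
| 0.7 | 0.1/0.714 = 0.14 | 11% | 8–9% | 4–6% |

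The signal also appears in TAU, so it is not specific to treatment. Further simulations with 58 per arm, means 60–65 and SDs 15–20, with no benefit or a constant 9-point benefit, widen the active-arm ranges to about 36–51% at r = 0.5, 20–30% at 0.6 and 8–15% at 0.7, with about 5% at 0.8. At r = 0.9 the association reverses, and low scorers are flagged in about 9–27% of trials.

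**Size for a purely prognostic variable.** In the 60-per-arm simulation, a variable with a standardised effect of 0.2, 0.3 or 0.4 on the post score, identical in both arms, is flagged in the active arm in 28–38%, 51–75% and 80–96% of trials (TAU: 22–27%, 44–55%, 67–82%). The interaction test again stays at 4–6%. A variable with no prognostic effect is flagged in about 5%. With 40 per arm, as in the biomarker substudy, at r = 0.6 and effect 0.3, the rates are 19% for baseline FIQR and 43% for the prognostic variable.

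**Precision of the alternative.** With 58 per arm and residual SD 1, the SE of an interaction slope is about √(2/58) = 0.186. For 80% power the slope difference must be about 2.8 × 0.186 = 0.52 SD per SD. Baseline adjustment at r = 0.6 gives a residual SD of √(1 − 0.36) = 0.8, so about 0.42.

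**The case against.** The analysis is labelled exploratory, and the statements about its use are hedged with words such as may and can. A reader might infer that prognostic variables and regression to the mean will be reported as predictors of benefit. The article does not go that far. It plans an exploration whose results can be misread, with no safeguard against the misreading. The aims sentence in 1.3 can also be taken to mean outcome while on a given treatment, which within-arm data can describe. The difficulty lies with the two Discussion statements, above all the one that equates responders with beneficiaries.

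A reader might also infer that high scorers simply regress past the threshold. They do not. Without treatment effect, the expected post score meets the rule only if pre ≥ μ(1 − r)/(0.8 − r). With mean 65 this is 108 at r = 0.5, 130 at 0.6 and 195 at 0.7, all beyond the scale maximum of 100. In simulation without effect, about 34–43%, 27–36% and 18–27% of patients more than 1 SD above the mean pass at those correlations, against 19–25%, 17–23% and 13–20% overall. High scorers are more likely to pass, but most do not.

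The sizes rest on inputs absent from the article, and both size and direction depend on the correlation. That stands.

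Benjamini–Hochberg correction is planned in the same section, although its scope over these tests is unclear. It limits chance findings. A prognostic association is real, so the correction cannot turn it into, or rule it out as, effect modification.

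**Conclusion.** The concern holds. Comparing responders with non-responders inside FIBRO-Out and FIBRO-On cannot distinguish prognosis or regression to the mean from effect modification, whatever the numbers turn out to be. The size of the distortion is conditional: for baseline FIQR, from about half of trials at a pre–post correlation of 0.5 down to the nominal 5% at 0.8, with the sign reversed above that; for other variables, it depends on how prognostic they are and is nil if they are not. All rates assume equal SDs, the stated FIQR mean and SD, and unadjusted tests at 0.05.

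The fault is confined to one exploratory analysis and the claims attached to it. The primary ITT comparison, the NNT, the mediation models and the cost-utility analysis are untouched. It is still worth correcting before analysis, because the Discussion ties the result to identifying beneficiaries and allocating resources.

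**What to change.** In section 2.11.1, add exploratory baseline-variable-by-arm interactions on FIQR in the ITT mixed model, using all three arms with TAU as reference, and report them as estimates with confidence intervals. Keep continuous baseline variables continuous. When baseline FIQR is itself the candidate, enter it as a covariate rather than as one of the repeated outcomes. Base any statement on who benefits from the programme on these interactions.

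If the within-arm tests are kept, label them prognostic only, and align the Discussion wording on beneficiaries and on matching treatments to patients with that label.

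The cost is wording and analysis code; no new data are needed. The downside is precision: at this sample size a slope difference of roughly 0.4–0.5 SD per SD is needed for 80% power, so the interaction estimates will be wide and fewer predictors will be claimed.
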